### Assessment of quality

The trial will be monitored by staff at the KEMRI-Wellcome Trust Programme’s Kilifi Clinical Trials Facility (KCTF), who will perform on-site and database monitoring. The approach for trial monitoring will include mentoring and supporting the trial staff and healthcare workers, working closely with them before, during and after the trial to help achieve an ethical, safe and accurate trial that answers the questions set within this protocol.

Pre-study start site visits will occur before the first participant is enrolled. Standard Operating Procedures (SOPs) will be developed followed by a study initiation visit that will be conducted by the study coordinator and supported by the monitoring staff from Kilifi. Here, the SOPs will be used to ‘walk’ through the study with everyone involved. All trial staff will be trained and certified for Good Clinical Practice (ICH-GCP). A trial monitoring plan will be written and signed off by the Trial Steering Committee. This will detail how many monitoring visits are planned and specify the key data points that require checking against source data. The fact that the products being used are known and safe, the trial is essentially open and there are no plans for interim analyses, internal monitoring being performed by KCTF staff [20] is in accord with WHO guidance [21].

### Data management

All protocol required information will be collected in Case Report Forms (CRF) designed by the investigators and KCTF. Data will be collected on paper proformas, will undergo a quality control step, and then be transcribed direct onto the trial data management system, OpenClinica. A random 10 % subset will be checked by the Ethiopia-based Data Manager. Data will be backed up daily onto secure external hard drives, and uploaded to the OpenClinica server at weekly intervals. Data management will be performed by the CTF in Kilifi, who operate an online OpenClinica data management system (Akaza Research, Waltham, MA). The trial monitor will visit for source data verification.

### Statistical methods

Statistical support will be provided by the KEMRI-Wellcome Trust Programme in Kilifi, Kenya. A detailed Statistical Analysis Plan will be developed in 2014-15 while the intervention is in process, and will be approved by the Trial Steering Committee. The main analysis will be a test of mean number of ADLA events by each arm over the observation period.

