### Sample size

We calculated the required sample size based on a mean (Standard Deviation) baseline incidence of ADLA of 5.6 (4.9) episodes/year reported in a survey conducted in November 2011 in this population [11]. We assumed a reduction in ADLA frequency of 28 % (from 5.6 to 4.0 episodes per year). Based on a sample size calculation for comparison of two means [16], a 90 % power, an α-level of 0.05, and a 40 % increase to enable adjustment for four confounders, and 15 % drop-out rate [9], that is, adjusting the sample size per group (206 × 1.4/0.85), we would need a total 680 patients: 340 patients in the immediate treatment arm and 340 patients in the control arm.

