### Randomisation

Initial community sensitisation through *woreda-* and *kebele-*level officials will be followed by Health Extension Workers enumerating patients in their respective *kebeles* selected for the study in the *woreda*. All patients identified by Health Extension Workers (HEWs) will be visited at home by a data collector and consent requested for preliminary evaluation against the inclusion and exclusion criteria. The data collector will record potential willingness to take part in the trial, Geographic Information System (GIS) coordinates of the house and local contact information (for example, *kebele* office, nearest mobile phone owner). Patients who appear to be eligible will then be given an appointment date for enrolment at the nearest health facility. At enrolment, all patients will be asked for full consent for the trial; be evaluated against inclusion and exclusion criteria once more, and ICT tests and baseline measurements will be carried out. Community Podoconiosis Assistants (CPAs), Data Collectors (DCs) and data supervisors assisted by the study coordinator and data manager, will enrol patients.

Data collectors will then map these patients by recording Geographic Information System (GIS) coordinates of their houses, generating a target list of approximately 850 potential trial participants and take consent to examine each listed patient. If more than one eligible patient is found in one household, one will be randomly selected using a lottery method. Using a sample frame of households within *kebeles*, a randomisation list will be prepared by statisticians at Kenya Medical Research Institute-Wellcome Trust Research Programme (KWTRP). Patients will be randomised in excess of the required sample size to allow for those who decline the invitation to participate or who are later found not to fulfil the inclusion criteria.

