### Intervention

The intervention in this trial is podoconiosis lymphoedema hygiene and foot-care management. This consists of monthly group meetings with instruction and practical demonstration of foot hygiene and foot care by Community Podoconiosis Assistants (CPAs), supporting daily self-treatment. In outline, ‘foot hygiene’ comprises soaking feet, washing with soap, rinsing with clean water, drying and application of emollient. ‘Foot care’ includes supervised use of single-layer, non-elastic bandages for disease stages ≥3; foot and calf exercises; instruction to practice foot hygiene daily at home; instruction to elevate the foot of the bed or areas slept on; instruction to use socks and shoes during waking hours. Those randomised to immediate treatment will receive a hygiene and foot-care intervention from December 2014 for one year, while those randomised to the control arm will be followed through 2014 and will be offered the intervention in 2015, unless it has been shown to be ineffective or harmful.

The trial interventions are described in Table 4.

**Table 4 Tab4:** Trial intervention

Action	Necessary items
Soak for 15 minutes	Bowl of water
Wash with soap	Named brand (GIV international white)
Apply emollient	Each patient will be issued with Whitfield’s ointment (2 tubes of 20 gm for a period of 1 month)
Apply bandages	For stage ≥3 disease; two short-stretch (<80 % stretch) bandages, spiral from foot, overlap 50 %, continue 8-10 cm above oedema
Elevation and exercises	Ankle rotation exercises.
	Elevate foot end of sleeping mattress, if used
Use socks and shoes	Temporary (tyre) shoes if bandages issued
	One pair robust, closed shoes and two pairs of socks after 3 months of treatment

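### The main ADLA analysis is written as an unadjusted comparison of arm means, although the sample was enlarged by 40% to support covariate adjustment

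*Protocol article*

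**What the plan says.** All references are to the protocol article.

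- **Statistical methods.** One sentence fixes the primary comparison: "The main analysis will be a test of mean number of ADLA events by each arm over the observation period". A detailed SAP is to follow while the intervention is under way.
- **Sample size.** The calculation rests on "mean (Standard Deviation) baseline incidence of ADLA of 5.6 (4.9) episodes/year" and "a reduction in ADLA frequency of 28 % (from 5.6 to 4.0 episodes per year", with "a 90 % power, an α-level of 0.05, and a 40 % increase to enable adjustment for four confounders" and a "15 % drop-out rate". The arithmetic is shown as "adjusting the sample size per group (206 × 1.4/0.85"), giving 340 per arm and 680 in total. The four confounders are not named.
- **Randomisation.** "Using a sample frame of households within *kebeles*, a randomisation list will be prepared" by the trial statisticians. No strata, blocks or minimisation are mentioned. The abstract describes allocation as individual, and Participants gives nine kebeles.
- **Intervention.** The package depends on stage, with "bandages for disease stages ≥3". Table 3 schedules clinical stage at baseline, in the same column as randomisation.

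**The concern.** Two sections describe the primary analysis differently. Sample size assumes an adjusted comparison and recruits for it. Statistical methods gives a comparison of means with nothing adjusted for. A reader cannot tell which is the primary analysis, and if the Statistical methods sentence is followed literally, the extra patients do not serve the purpose given for recruiting them.

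The protocol already holds two natural covariates. Kebele is in the sampling frame, and stage is measured at baseline and determines part of the package. If either predicts ADLA frequency, an unadjusted test leaves that variation in the error term. What is at stake is some precision and a clear primary analysis, not the validity of the comparison.

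Timing adds to the case for settling it. The Blinding section says that the analysing statisticians cannot be blinded and that the analysis plan will be defined during the intervention period. Covariates chosen late in an open trial are easier to criticise as data-driven.

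**Working it through.** **1. Reproduce the plan's sample size.** Inputs from Sample size: mean 5.6, SD 4.9 (applied to both arms), 28% reduction, 90% power, alpha 0.05. Sidedness is not stated; two-sided reproduces the figure.

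- Difference: 0.28 × 5.6 = 1.568.
- n per arm = 2 × (1.960 + 1.282)² × 4.9² / 1.568², which rounds up to 206. This matches. The rounded difference 5.6 − 4.0 = 1.6 would give 198, so the plan used the exact 28%.
- With both inflations: 206 × 1.4 / 0.85 = 339.3, so 340 per arm and 680 in total. This matches.

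**2. What the 1.4 buys.** Without it, 206 / 0.85 = 242.4, so 243 per arm. The difference is 340 − 243 = 97 per arm, or 194 of 680 patients.

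**3. Precision of the test as written.** Evaluable per arm: 340 × 0.85 = 289. SE = 4.9 × √(2/289) = 0.408 episodes. Power is 97.5% for a difference of 1.6 (97.0% for 1.568).

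**4. What adjustment would add.** Let R² be the share of outcome variance explained by the covariates. The documents give no value, so 0.02 to 0.20 is an assumed range. Adjusted SE = 0.408 × √(1 − R²), ignoring the few degrees of freedom spent on the covariates.

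| Assumed R² | Adjusted SE | SE reduction | Power for 1.6 |
|---|---|---|---|
| 0 | 0.408 | none | 97.5% |
| 0.02 | 0.404 | 1.0% | 97.7% |
| 0.05 | 0.397 | 2.5% | 98.1% |
| 0.10 | 0.387 | 5.1% | 98.5% |
| 0.20 | 0.365 | 10.6% | 99.2% |

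**5. Is the unadjusted test valid?** That depends on an allocation detail the article does not state.

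- *Simple allocation.* The unadjusted SE is correct. In a simulation with 578 patients in nine near-equal kebeles, type I error was 0.050 when kebele explained 5% of variance and 0.049 when it explained 10%.
- *Allocation stratified by kebele.* The unadjusted SE is too wide by the factor 1/√(1 − R²), where R² is now the kebele share only. The approximate true level is 2 × (1 − Φ(1.96/√(1 − R²))), which is 0.044 at 5% and 0.039 at 10%. The simulation gave 0.044 and 0.042. Both are below 0.05, so the test is conservative.

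**The case against.** The best defence is that one summary sentence in a condensed article does not exclude adjustment. Sample size plainly foresees it, the four covariates may well include kebele or stage, and covariate lists are commonly left to the SAP. This stands in part: not naming the covariates in the article is not a fault. It does not remove the mismatch, because the one sentence that defines the main analysis describes something other than what the sample was sized for.

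It is also fair to say that little power is at risk, since the plan's own assumptions already give about 97.5%. That stands, and it makes this a minor point.

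A reader might go further and infer that the confidence interval does not match the design because patients are randomised within kebeles. The documents do not support that. The Randomisation section describes a sampling frame and never states stratification. On one reading of it the unadjusted SE is valid, and on the other it errs on the safe side.

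Nor does a package that varies with stage invalidate the standard error. Stage-dependent bandaging is part of a single strategy compared with delayed treatment, and stage matters here only as a possible predictor of ADLA. Stage is not a stratum on any reading, so variance explained by kebele and stage together cannot be used to size an error in the test's level.

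**Conclusion.** The point holds as an inconsistency between two sections with a small, avoidable loss of precision. Sample size adds about 97 patients per arm for covariate adjustment, and Statistical methods states a main analysis without any. The comparison is not biased and its type I error is not inflated.

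The gain from adjusting is about 1% to 11% in the standard error and 0.2 to 1.7 points of power. This rests on an assumed R² of 0.02 to 0.20, SD 4.9 in both arms and 289 evaluable patients per arm. If kebele and stage explain almost nothing, the gain is close to nil, but the two sections still disagree.

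A reader might also conclude that the allocation should be re-stratified by kebele and stage. That does not follow. It would be a design preference, Trial status reports that recruitment began on 8 October 2014, and the Randomisation section allows patients to be randomised in excess before eligibility is fully settled.

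**What to change.** Amend the main-analysis sentence in Statistical methods, and carry the change into the SAP, so that:

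1. the primary ADLA comparison comes from a model with arm and pre-specified baseline covariates, including kebele (as a factor) and baseline clinical stage (2 versus 3 or above);
2. all covariates covered by the 40% allowance are named before outcome data are examined by arm;
3. the unadjusted test of means is kept as a sensitivity analysis.

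Add one sentence to Randomisation saying whether kebele is a stratum of the list.

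The cost is two or three sentences. Kebele comes from the sampling frame and stage from the scheduled baseline visit, so no new data are needed. The sample size and the allocation procedure stay as they are.

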### Ethical approval

The study is approved by the Research Governance and Ethics Committee of the University of Sussex (approval number 13/107/DAV; approval date: 12/08/2014), College of Health Sciences, Addis Ababa University (meeting number 056/2014; protocol number 071/13/SPH; approval date: 12/01/2014), the Food, Medicine and Health Care Administration and Control Authority (reference number 02/6-1/05/39; approval date: 09/04/2014) and the National Research Ethics Review Committee of the Ministries of Health and Science and Technology in Ethiopia (approval number 3-1/794/06; approval date: 02/06/2014).

## Discussion

Limited evidence exists for the effectiveness of lymphoedema care similar to that used for filarial lymphoedema. To date, one non-controlled follow-up study among podoconiosis patients indicated improvements in quality of life measures very rapidly (within the first 3 months), but slower clinical changes (leg circumference and stage of disease), with statistically significant changes being observed after 6-9 months of follow-up [9]. However, there are no published controlled clinical trials investigating the effectiveness of lymphoedema management in podoconiosis. We have therefore designed a full-scale trial to interpret the results to understand the timing of clinical changes and their relationship to psychosocial changes in order to be able to advise the optimal duration of supervised treatment. Our study will be the first fully controlled, pragmatic trial of the intervention, with measurement of a wider range of outcomes, including frequency of acute dermatolymphangioadenitis (ADLA) in podoconiosis lymphoedema. The evidence is highly likely to inform implementation of the new master plan for integrated control of Neglected Tropical Diseases (NTDs), in which podoconiosis is identified as one of eight NTDs prioritised for control. Potentially, an estimated 3 million patients in Ethiopia will therefore benefit from the results of this trial.

## Trial status

The Rapid Ethical Assessment, the economic context survey and validation of the patient-held diary have all been completed. Recruitment for the trial commenced on 8 October 2014.

## Abbreviations

ADLA: acute dermatolymphangioadenitis
CRF: case report form
CPA: Community Podoconiosis Assistant
DLQI: Dermatology Life Quality Index
DSMB: Data Safety Monitoring Board
ICH-GCP: International Conference on Harmonisation - Good Clinical Practice
IOCC: International Orthodox Christian Charities
KCTF: Kilifi Clinical Trials Facility
KWTRP: Kenya Medical Research Institute-Wellcome Trust Research Programme
LSM: Local Safety Monitor
NTD: Neglected Tropical Diseases
NGO: non-governmental organisation
REA: Rapid Ethical Assessment
SAE: serious adverse event
SUSAR: suspected and unsuspected serious adverse reaction
WHODAS: World Health Organisation Disability Assessment Schedule
